### 2.3. Data Collection

#### 2.3.1. Human Samples

Table 2 provides an overview of the methods that will be used in each country to collect different types of samples. Healthy individuals will be asked to self-sample and/or to have throat, navel, and rectal/perianal swabs taken once after providing informed consent. Self-sampling kits, which can be send to healthy individuals’ homes, contain an information letter, step-by-step instructions (including images and links to online videos), and self-sampling materials to assist in taking the required swabs correctly [22]. Healthy individuals can provide the swabs immediately during a home visit or live event, or return the swabs by regular mail. For healthy individuals, the distance of each individual’s home to the water sampling locations will be calculated by a Python script using the distance between the centric point of the zip code area to the mWWTP, and river upstream and downstream sampling locations.

After obtaining informed consent, throat, navel, and rectal/perianal swabs will be taken once from the patients within the first 48 h of their admission. Patients will also be allowed to self-sample after receiving verbal instructions from a member of the research team. Clinical CRPA isolates will be collected in the routine diagnostics laboratories of each hospital. Additionally, basic patient characteristics and admission information will be collected from the (electronic) health records of all patients (including the patients from whom the clinical CRPA isolates originate), such as age at admission, sex, and type of ward. All of the human data will be collected and stored on the online platform Castor, with the metadata presented in Supplementary Table S1.

#### 2.3.2. Questionnaire

A questionnaire was developed by a subgroup of the SAMPAN Consortium, including a clinical microbiologist and an epidemiologist. Questions related to known risk factors of CRPA carriage during hospitalization (e.g., the presence of underlying diseases, antibiotic use, having medical devices, etc.) are based on a study by Voor in ‘t holt et al. [23], and questions related to drinking water and sanitation are based on a guidance document by the WHO and the United Nations Children’s Fund (UNICEF) [24]. In total, the questionnaire contains 37 questions, and consists of 6 general questions, 10 questions related to the participant’s health, 3 questions related to international travel, and 18 questions related to contact with water. The questionnaire was developed in English and was subsequently translated into Dutch, Italian, and Indonesian, and is only available on paper for the participants. Healthy individuals and patients, and, when possible, patients from whom the clinical CRPA isolates are collected, will receive the same questionnaire (with the options for different languages) (Supplementary File S2).

#### 2.3.3. Environmental Samples

The hospital environment will be sampled twice throughout the study period, once at the beginning and once at the end of the sampling year. Samples will be collected from the sink drains and shower drains in all of the patient rooms, including their attached (private) bathrooms, from the wards in which the patients will be enrolled for study participation. Additional sampling sites were chosen per hospital based on potential ‘high-risk’ reservoirs for CRPA. Supplementary File S1 (Figures S1–S3) provides an overview of the sampling sites in each hospital. The sampling methods described by Van der Schoor et al. will be used to collect the samples [25]. In brief, a sterile cotton swab will be pre-moistened using phosphate-buffered saline (PBS). For the sink drains, the cotton swab will be inserted 1–3 cm inside of the drain, followed by sampling the inner surface of the drain pipe while rotating the swab. In the case where a plug covering the sink drain is present, the swab will be inserted underneath the sink plug to sample the inner sink environment. The outer surface of the shower drain will be sampled in multiple directions while rotating the swab and using overlapping motions.

Water samples will be taken once per month from a variety of sampling sites (Table 2). Inside of the hospitals, the sampling sites include the (drinking) water inlet, and the influent and effluent of the hWWTP(s) (where existing), where the raw sewage from the hospital is collected and treated before discharge into the receiving river (Indonesia) or into the municipal sewer network leading to the mWWTP (The Netherlands). Outside of the hospitals, the samples will be collected from the influent and effluent of the receiving mWWTP (The Netherlands and Italy) or an mWWTP in proximity (Indonesia), as well as river upstream and downstream of the discharge point of the hWWTPs/mWWTP. Different methods will be used to collect water samples depending on the accessibility of the sampling site. Grab samples will be taken from, e.g., a tap point for the (drinking) water inlet, a basin, and river upstream and downstream of the hWWTPs/mWWTP, with the latter by the use of a telescope pole with an attached beaker. Sampling will follow the standardized EN ISO 16266 methods [26]. In the Netherlands, 24-h flow proportional samples using automated samplers will be taken from the influent of the hWWTP, and from the influent and effluent of the mWWTP. Supplementary File S1 (Figures S4–S9) provides an overview of the sampling locations in each city as well as schematics of the hospital wastewater treatment systems. Samples will be collected by researchers from the study group and/or staff from the mWWTPs. Subsequently, water samples will be transported to the laboratory, while stored at 4 °C, on the day of sample collection and analyzed within 24 h.

### 2.4. Microbiological Methods

#### 2.4.1. Samples from Healthy Individuals and Patients upon Hospital Admission

The culture methods, as described in Shahab et al. [27,28], will be used for the samples from healthy individuals and patients upon hospital admission. In short, rayon swabs (Thermo Scientific™ Oxoid™ Amies Agar Gel Transport Swabs, ThermoFisher Scientific, Breda, The Netherlands) will be used to collect throat, navel, or rectal/perianal swabs. The swabs will be enriched in Tryptic Soy Broth (TSB) with 2 mg/L vancomycin and 2 mg/L imipenem as selective agents by adding disks to the broth, followed by overnight incubation at 35 °C. Vancomycin is added to the broth to suppress the growth of Gram-positive bacteria. The choice of imipenem as a selective agent is based on MIC considerations, with imipenem being more often resistant than meropenem in important CRPA clones, as well as the finding that imipenem in disks is more stable than other carbapenems [27,29,30]. Subsequently, 10 µL of the broth will be inoculated onto a *Pseudomonas*-selective agar, M-PA-C agar (BD Diagnostics, Breda, The Netherlands), and incubated at 35 °C for 18–24 and 48 h.

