Secondly, we aim to enroll 500 hospitalized patients in each city over a period of one year. Similarly, the lack of prevalence data among newly hospitalized patients prevents accurate sample size determination. Patients will be asked to participate within the first 48 h of their admission to the hospital. All of the patients from non-critical medical and surgical wards are eligible for inclusion if they are aged 18 years or older, if they have an expected length of stay of at least 24 h, if they can provide answers to a questionnaire verbally or in writing, and if they have a signed informed consent sheet. Patients will only be included once during the inclusion period. Patients that are unwilling to provide a rectal/perianal swab and patients with cystic fibrosis (CF) are excluded from study participation. The enrolment progress of healthy individuals and newly hospitalized patients will be monitored closely by the central study coordinators ([name] and [name]) in order to ensure the highest possible number of participants.

Clinical CRPA isolates from patients throughout the entire hospital, as identified through routine diagnostics, will also be collected. Only one CRPA isolate per patient will be included. If multiple CRPA isolates are available from the same patient, the first isolate will be included. If more than one isolate is available from that same date, the most resistant CRPA isolate (i.e., the highest MIC and/or resistance to a wider range of antibiotics) will be included. Clinical CRPA isolates from CF patients are not eligible for inclusion.

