#### 2.4.2. Hospital Environment Samples

Sterile cotton swabs will be used to collect samples from the wet hospital environment and, after sample collection, will be enriched in TSB with 2 mg/L vancomycin and 2 mg/L imipenem. After overnight incubation at 35 °C, 10 µL of the broth will be inoculated onto M-PA-C agar, followed by incubation at 35 °C for 18–24 and 48 h.

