#### 2.4.3. Water Samples

For the isolation and quantification of CRPA from the water samples, a most probable number (MPN) method will be used, based on filtrations of the water samples. The filtered volumes used in each sampling site are shown in Supplementary Table S2, including a range of volumes with both expectedly negative and expectedly positive results as required for the MPN method. The methods to detect CRPA in water samples have previously been described [31]. Briefly, water samples will be filtered through 0.45 µm pore size membrane filters (Millipore, Burlington, MA, USA). The filters will then be placed in 10 mL Asparagine Proline (ASP) broth (Millipore, Burlington, MA, USA) with 2 mg/L vancomycin, followed by incubation for 18–24 h at 37 °C. After incubation, 10 µL of the enrichment broth will be inoculated onto M-PA-C agar supplemented with 8 mg/L imipenem. After incubation for 18–24 h at 37 °C, presumptive *P. aeruginosa* colonies will be streaked onto the M-PA-C agar and again incubated for 18–24 h at 37 °C. The number of colonies picked is based on the observed number of colony morphologies on the plates, as detailed in Supplementary Table S3. Colonies growing on the M-PA-C agar will then be streaked onto Columbia agar with sheep blood (Oxoid, Basingstoke, UK) and incubated for 18–24 h at 37 °C.

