#### 2.4.5. Identification and Antimicrobial Susceptibility Testing

In Jakarta, preliminary identification will be performed by an oxidase test, followed by the identification of all oxidase-positive isolates, using the Vitek^®^2 with a GN Identification Card (bioMérieux, Marcy L’Etoile, France). In Rotterdam and Rome, species-level identification will be performed on all presumptive *P. aeruginosa* colonies using Matrix-Assisted Laser Desorption Ionization–Time-of-Flight Mass Spectrometry (MALDI-TOF MS [Bruker Daltonics, Bremen, Germany]). Antibiotic susceptibility tests will be performed by the Vitek^®^2 with the AST-GN Card in all three cities. However, the AST-GN Card available in Indonesia does not include imipenem in the panel; therefore, disk diffusion for imipenem and meropenem will also be performed in Jakarta. Susceptibility test results will be interpreted according to the Clinical & Laboratory Standards Institute (CLSI) guidelines [32]. CRPA was defined as resistance to at least one of the carbapenems tested (i.e., MIC ≥ 8 for imipenem and/or meropenem). All of the CRPA isolates will be stored at −80 °C prior to further processing.

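### Swabs are recovered only through 2 mg/L imipenem broth, so CRPA with low imipenem MIC but meropenem resistance can enter the clinical set and not the swab sets

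*Protocol article*

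**What the plan says.** All places are in the protocol article.

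- **Swabs from healthy individuals and admission patients (2.4.1).** "The swabs will be enriched in Tryptic Soy Broth (TSB) with 2 mg/L vancomycin and 2 mg/L imipenem as selective agents". After overnight incubation the broth is plated "onto a *Pseudomonas*-selective agar, M-PA-C agar", with no carbapenem in the agar stated. The reasons given for imipenem are "imipenem being more often resistant than meropenem in important CRPA clones" and its better stability in disks.
- **Drain swabs (2.4.2).** These "will be enriched in TSB with 2 mg/L vancomycin and 2 mg/L imipenem" and are plated in the same way.
- **Case definition (2.4.5).** "CRPA was defined as resistance to at least one of the carbapenems tested (i.e., MIC ≥ 8 for imipenem and/or meropenem"). Resistance to meropenem alone is enough.
- **Clinical isolates (2.2).** "Clinical CRPA isolates from patients throughout the entire hospital, as identified through routine diagnostics, will also be collected". No imipenem enrichment is described for them.
- **Limitations (Discussion).** Geography and non-response are named. Selection by a single carbapenem is not.

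**The concern.** The case definition accepts resistance to either carbapenem, but the swab method filters on one of them before any susceptibility test is done. An isolate that does not survive the broth cannot be classified later. The clinical set, as described, does not pass through that filter.

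Two of the study's aims are touched. Aim 1 is the carriage rate of CRPA; with this method the swabs measure CRPA that grows in 2 mg/L imipenem, which is a slightly smaller set than CRPA as defined. Aim 3 compares isolates between reservoirs to support possible transmission routes. There, a difference in what each reservoir can yield acts in one direction only: it reduces the chance of finding a swab counterpart for some clinical isolates, and a larger sample does not correct it. If the mix of resistance patterns differs between Rotterdam, Rome and Jakarta, the loss could differ between cities too. These results then inform the Delphi rounds on which reservoirs to monitor (2.5).

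**Working it through.** The plan gives no figure for this point, so there is none to reproduce. The check is a comparison of thresholds, followed by an illustration.

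**Step 1: thresholds.** Inputs: broth at 2 mg/L imipenem (2.4.1, 2.4.2); CRPA at MIC of 8 or more for either drug (2.4.5). Nominal rule: a strain grows in broth at concentration c only if its MIC exceeds c.

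| Imipenem MIC | Meropenem MIC | CRPA by 2.4.5 | Grows in the swab broth | Can enter the clinical set |
|---|---|---|---|---|
| 8 or more | any | yes | yes | yes |
| 4 | 8 or more | yes | yes | yes |
| 2 or less | 8 or more | yes | no | yes |

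The broth lies two doubling dilutions below the cut-off (8 to 4 to 2). Only the last row is lost, which is a part of the meropenem-only group and not all of it.

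**Step 2: what the loss could do to carriage.** Input from the plan: N = 500, the target stated for healthy individuals and, per city, for admission patients (2.2). The rest are assumptions, because the document gives no values:

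- p = true CRPA carriage, 1% to 5%
- m = share of CRPA that is meropenem-resistant with imipenem MIC below 8, 2% to 10%
- u = share of those with imipenem MIC of 2 or less, 0 to 1

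Expected missed carriers = N × p × m × u. Half-width of the 95% interval = 1.96 × √(p(1 − p)/N).

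| p | m | u | True carriers | Missed | Observed carriage | Half-width (points) |
|---|---|---|---|---|---|---|
| 1% | 2% | 0.5 | 5 | 500 × 0.01 × 0.02 × 0.5 = 0.05 | 0.99% | 0.87 |
| 2% | 5% | 1 | 10 | 500 × 0.02 × 0.05 × 1 = 0.5 | 1.90% | 1.23 |
| 5% | 10% | 1 | 25 | 500 × 0.05 × 0.10 × 1 = 2.5 | 4.50% | 1.91 |

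With u = 0 nothing is missed, so the range is 0 to 2.5 per 500. If the lost share m × u were as high as 20%, at p = 5%, then 25 × 0.20 = 5 carriers would be missed and 4.0% observed instead of 5.0%. That is still a smaller shift than the half-width of 1.91 points.

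**Step 3: what it could do to the comparison between reservoirs.** If clinical isolates have the same mix of resistance patterns (a further assumption), a share m × u of them, 0 to 10% over the grid above, belongs to a phenotype that swabs cannot yield. Nominal recovery of CRPA in swabs relative to clinical isolates is 1 − m × u, or 1.00 down to 0.90. Among isolates with imipenem MIC of 8 or more on both sides, this filter removes nothing from either, so the ratio is 1.

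**The case against.** The choice of imipenem is deliberate and reasoned, with two grounds given and source methods cited. As a single selective agent it is defensible, and the stated resistance pattern suggests that few strains are lost. The possible effect on carriage rates lies well inside sampling error. All of this stands, and it is why the culture method should be kept and why the point is a modest one.

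Several stronger readings are tempting, and the document does not support them.

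- *That all meropenem-only carriers are missed.* Strains with imipenem MIC 4 grow in the broth and are then classed as CRPA.
- *That the plan's own rationale admits the lost phenotype.* "imipenem being more often resistant than meropenem in important CRPA clones" is also true if every meropenem-resistant isolate is imipenem-resistant. It says nothing about strains with imipenem MIC of 2 or less.
- *That carriage and clinical CRPA are two different phenotypes.* One MIC definition is stated. What differs is the sensitivity for one subgroup.
- *That clinical isolates are unselected.* The routine diagnostic media are not described. One can say only that no imipenem step is stated.
- *That every affected clinical isolate will appear to have no source.* Relatedness is to be judged on clonality, resistance genes and mobile elements by whole-genome sequencing (Introduction, aims; 2.4.6). Such an isolate can still match a swab isolate of the same clone with a higher imipenem MIC. The chance of a match falls; it does not vanish.

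Water is a related case. There the colonies are "inoculated onto M-PA-C agar supplemented with 8 mg/L imipenem", which nominally suppresses the whole meropenem-only group. That mismatch is sharper, but it does not remove the one between swabs and clinical isolates.

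**Conclusion.** The mismatch is in the text and holds in a limited form. CRPA with imipenem MIC of 2 or less and meropenem MIC of 8 or more meets the definition, is nominally undetectable in swabs from people and drains, and can enter the clinical set. The direction is under-detection in swabs relative to clinical isolates.

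The size cannot be computed from the document, because it gives neither CRPA carriage nor the share of this phenotype. Under the assumptions shown, 0 to 2.5 carriers per 500 are missed, which is small beside sampling error. The firmer ground is the comparison between reservoirs, where the difference is systematic, together with the accuracy of the carriage label. The conclusion rests on the nominal growth rule and on the absence of any described imipenem selection in routine diagnostics. It is a cheap improvement and not a flaw that threatens the study.

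**What to change.** 1. Keep the culture method.
2. State in 2.4.1 and 2.4.2, and among the limitations, that swab carriage and drain positivity mean CRPA detected under 2 mg/L imipenem selection, and that meropenem-resistant strains with low imipenem MIC may be missed.
3. Run the comparisons of clinical isolates with carriers and drains on imipenem-resistant isolates on both sides: imipenem MIC of 8 or more, or the CLSI resistant category by disk diffusion in Jakarta, where the card lacks imipenem. The restriction must be symmetric. Applied to clinical isolates alone, it would drop meropenem-only isolates there while keeping those that swabs do recover, and so create a new mismatch.
4. Report meropenem-only isolates from any reservoir as a separate group.

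The cost is wording and an analysis subset. The susceptibility results needed are already planned in 2.4.5, so no sample, culture or test is added. The downside is a slightly narrower carriage claim and fewer isolates in the restricted comparison.

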#### 2.4.2. Hospital Environment Samples

Sterile cotton swabs will be used to collect samples from the wet hospital environment and, after sample collection, will be enriched in TSB with 2 mg/L vancomycin and 2 mg/L imipenem. After overnight incubation at 35 °C, 10 µL of the broth will be inoculated onto M-PA-C agar, followed by incubation at 35 °C for 18–24 and 48 h.

#### 2.4.3. Water Samples

For the isolation and quantification of CRPA from the water samples, a most probable number (MPN) method will be used, based on filtrations of the water samples. The filtered volumes used in each sampling site are shown in Supplementary Table S2, including a range of volumes with both expectedly negative and expectedly positive results as required for the MPN method. The methods to detect CRPA in water samples have previously been described [31]. Briefly, water samples will be filtered through 0.45 µm pore size membrane filters (Millipore, Burlington, MA, USA). The filters will then be placed in 10 mL Asparagine Proline (ASP) broth (Millipore, Burlington, MA, USA) with 2 mg/L vancomycin, followed by incubation for 18–24 h at 37 °C. After incubation, 10 µL of the enrichment broth will be inoculated onto M-PA-C agar supplemented with 8 mg/L imipenem. After incubation for 18–24 h at 37 °C, presumptive *P. aeruginosa* colonies will be streaked onto the M-PA-C agar and again incubated for 18–24 h at 37 °C. The number of colonies picked is based on the observed number of colony morphologies on the plates, as detailed in Supplementary Table S3. Colonies growing on the M-PA-C agar will then be streaked onto Columbia agar with sheep blood (Oxoid, Basingstoke, UK) and incubated for 18–24 h at 37 °C.

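### The water plate selects at 8 mg/L imipenem, above the inclusive CRPA threshold and the 2 mg/L used for swabs, so some isolates that count as CRPA can be recovered from swabs but are largely suppressed in water

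*Protocol article*

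**What the plan says.** The Protocol article gives one case definition, in section 2.4.5, with no version specific to a reservoir: "CRPA was defined as resistance to at least one of the carbapenems tested (i.e., MIC ≥ 8 for imipenem and/or meropenem". The culture step that decides which isolates reach that test differs by reservoir.

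- **Water (section 2.4.3).** Enrichment is in "Asparagine Proline (ASP) broth (Millipore, Burlington, MA, USA) with 2 mg/L vancomycin", with no carbapenem. The broth is then "inoculated onto M-PA-C agar supplemented with 8 mg/L imipenem". That plate is the only carbapenem selection in the water method, and it also yields the MPN.
- **Healthy individuals and admitted patients (section 2.4.1).** Swabs go into broth with "2 mg/L vancomycin and 2 mg/L imipenem as selective agents by adding disks to the broth", then onto M-PA-C agar for which no imipenem is stated.
- **Hospital environment (section 2.4.2).** Swabs are "enriched in TSB with 2 mg/L vancomycin and 2 mg/L imipenem", then plated in the same way.
- **Clinical isolates (section 2.2).** These come from routine diagnostics, with no study selective medium described.

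Section 2.4.1 explains why imipenem was chosen as the agent in the swab broth. The article gives no reason for a higher concentration in water. Section 2.4.4 aligns methods between countries, not between reservoirs.

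**The concern.** The MIC is the lowest concentration that stops growth. The definition includes an imipenem MIC of exactly 8, yet such an isolate is expected not to grow on a plate containing 8 mg/L. The water method therefore starts one doubling dilution above the study's own imipenem threshold. It also works against isolates that qualify through meropenem alone. An isolate that never forms a colony cannot be classified by the testing in section 2.4.5.

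The third aim (section 1) uses genetic relatedness between reservoirs to confirm possible transmission routes, and section 2.5 feeds the findings into the Delphi process. If a human isolate lies in the range that the water plate suppresses, a missing water match may come from the medium and be read as absence of transmission. The error runs in one direction, and more samples do not remove it.

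**Working it through.** No figure in the article can be reproduced here. The check sets the thresholds side by side and then shows what an assumed loss would do.

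**Inputs.** CRPA: imipenem MIC ≥ 8 or meropenem MIC ≥ 8 (section 2.4.5; no unit is printed, mg/L is assumed). Swab selection: 2 mg/L imipenem (2.4.1, 2.4.2). Water selection: 8 mg/L imipenem (2.4.3).

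**Rule.** An isolate grows at imipenem concentration c only if its imipenem MIC > c. On doubling dilutions, growth at 2 mg/L needs an MIC ≥ 4, and growth at 8 mg/L needs an MIC ≥ 16.

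**Step 1: which CRPA can be recovered.** Take both MICs on the grid 0.5, 1, 2, 4, 8, 16, 32, which has 7 × 7 = 49 combinations. Non-CRPA needs both MICs ≤ 4: 4 × 4 = 16. CRPA combinations: 49 − 16 = 33.

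| Imipenem MIC | Meropenem MIC | Combinations | Swab broth, 2 mg/L | Water plate, 8 mg/L |
|---|---|---|---|---|
| ≥ 16 | any | 2 × 7 = 14 | grows | grows |
| 8 | any | 1 × 7 = 7 | grows | suppressed |
| 4 | ≥ 8 | 1 × 3 = 3 | grows | suppressed |
| ≤ 2 | ≥ 8 | 3 × 3 = 9 | suppressed | suppressed |

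Swabs can recover 14 + 7 + 3 = 24 of 33 combinations and water 14 of 33. The difference specific to water is 7 + 3 = 10 combinations. The last 9 are suppressed in swabs and water alike and enter mainly through routine clinical isolates. These are counts of combinations, not prevalences.

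**Step 2: effect on water results.** Let f be the share of CRPA in water, by the study's definition, that does not grow on the plate. With Poisson counts and a mean of λ CRPA per filtered volume, the expected MPN is multiplied by (1 − f), the log10 bias is log10(1 − f), and the chance that a volume is positive is 1 − exp(−λ(1 − f)). The article gives no value for f; the range below is an assumption. With λ = 1 and f = 0, the chance is 1 − exp(−1) = 0.632.

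| Assumed f | MPN ratio | log10 bias | Chance positive, λ = 1 |
|---|---|---|---|
| 0.05 | 0.95 | −0.022 | 0.613 |
| 0.10 | 0.90 | −0.046 | 0.593 |
| 0.20 | 0.80 | −0.097 | 0.551 |
| 0.30 | 0.70 | −0.155 | 0.503 |
| 0.50 | 0.50 | −0.301 | 0.393 |

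This f says nothing direct about the share of human isolates whose water match would be missed. That share belongs to a different population and is also unknown.

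**The case against.** Five counter-arguments deserve an answer.

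- **Not every other reservoir is affected.** A reader might infer that water misses isolates that all other reservoirs pick up. That holds for imipenem MIC 8, and for imipenem MIC 4 with meropenem ≥ 8. It does not hold for meropenem-resistant isolates with imipenem MIC ≤ 2: the swab broth suppresses those as well, so only routine clinical isolates differ.
- **MPN is not compared across reservoirs.** Only water is quantified. Water sites and months are compared on one medium, so the MPN bias concerns the label CRPA and not a contrast with swabs. This stands.
- **Suppression is not absolute.** The plate receives 10 µL of enrichment broth, and CRPA status comes from Vitek or disk diffusion, so growth and reported MIC need not agree near the breakpoint. Relatives of a human isolate with MIC 8 may also have higher MICs and grow. A reader might infer that such a clone has almost no chance of being found in water; the documents do not support that.
- **The article is condensed.** The water method is cited as described before, and a rationale for 8 mg/L may exist there. That could justify the choice, but it would not remove the mismatch between two concentrations and a definition that are all printed here.
- **A lower concentration has its own cost.** The plate is the only carbapenem selection for water, and the number of colonies picked depends on the morphologies seen. At a lower concentration, non-CRPA colonies could take the picks and create false-negative volumes. This stands, and it is why the fix below rests on the analysis.

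**Conclusion.** The concern holds in a limited form. Isolates with imipenem MIC 8, or imipenem MIC 4 with meropenem MIC ≥ 8, meet the study's definition and can be recovered from swabs, but are expected to be largely suppressed in water. Against that definition, water positivity and water MPN are biased low, water isolates lean towards high imipenem MICs, and human-water links can be hidden.

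The size cannot be determined from the article. The bias of 0.02 to 0.30 log10 rests wholly on an assumed loss of 5% to 50%, on the usual meaning of MIC and on a Poisson model. For counts this is modest; the more serious consequence is for how a missing human-water match is interpreted. The article does not show that such links are lost altogether, nor that trends within water are distorted by the difference in selection between reservoirs.

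**What to change.** **In the analysis.** Repeat the cross-reservoir comparisons of positivity and relatedness on the set that both methods can recover, and report them beside the all-CRPA results. Where an imipenem MIC exists, the set is MIC ≥ 16 mg/L. In Jakarta the Vitek card lacks imipenem and disk diffusion is used, so membership could be decided by growth of stored isolates (section 2.4.5 keeps all CRPA at −80 °C) on the same 8 mg/L plate. Otherwise, report Jakarta separately. Deciding by plate growth in one city and by MIC in the others is itself a method difference and should be stated.

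**In the wording.** Describe water positivity and MPN as CRPA growing at 8 mg/L imipenem, and state the different selective thresholds as a limitation.

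**Cost.** The common set is smaller, and Jakarta needs some re-plating or a separate report.

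**If water sampling has not started.** The laboratory could consider a sub-breakpoint imipenem level on the water plate and let susceptibility testing decide CRPA status, as for the swabs. The colony-picking rule should first be checked for overgrowth by non-CRPA colonies.
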